### 2.6. Procedure

Background data on age, sex, method of surgery for the hip fracture, and medication will be collected at baseline. All other measures will be collected at baseline and end of the rehabilitation period. Postural sway and balance will also be assessed 3 months after the end of the rehabilitation period. At the end of the rehabilitation period, physiotherapists fill in USEQ and also record how many home visits were performed and time spent at each home visit as well as the number of phone-calls each participant required.

Baseline data, including information about age, sex, method of surgery for the hip fracture, and medication, as well as outcome measures, will be obtained by a PT at a regular home visit. Follow-up measures will be performed at the end of the rehabilitation period, including primary and secondary outcome measures. The rehabilitation period is defined by the needs of the individual participant and can hence differ in time between participants.

At the end of the intervention treatment, the PTs will fill in the USEQ questionnaire regarding how satisfied they were with using the information from the IMU. During the study, PTs will document the duration and number of home visits as well as telephone calls. PTs time and number of visits is not a pre-designed factor, and it will adapt to the patient’s necessities. The treating PT will also take notes regarding participants who discontinue or deviate from the intervention’s protocols, including reasons for discontinuing or deviating.

All PTs in community healthcare in Malmö, who rehabilitate persons with hip fracture in the Malmö municipality, have received education in the HIFE program. Additionally, workshops including an introduction of the IMU, how to use it, and how to retrieve data from it have been performed. Inclusion of participants to the pilot and feasibility study started in May 2021 and is expected to be completed in December 2021. After that, any necessary changes to the study protocol will be made and a decision whether the full RCT should be conducted will be made.

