### 2.4. Interventions

In order to increase the usefulness of the results from this RCT, all three groups receive interventions that are tailored to each participant, after assessment by a PT, either within the specified frame of standard rehabilitation (control group) or HIFE (intervention A and B). Additionally, the rehabilitation time periods are tailored to each participant in order to adjust the study to a clinical setting. However, a minimum number of sessions as well as a time interval for the rehabilitation period will be defined after analysis of the results collected in the planned pilot and feasibility study.

Control group: the intervention comprises the standard rehabilitation services: walking training and adaptions to the walking pattern of the patient prior to surgery together with functional exercises [30]. The intervention is tailored to each patient, based on the type of fracture, type of surgery, and assessment by the PT as well as treatment goals.

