Intervention A: the intervention comprises the HIFE protocol and, if necessary, other additional exercises. HIFE consists of five exercise categories depending on the capabilities of the patient. A task of walking a short distance (5–10) meters without aid works as a guideline for the PT to select the most suitable exercises for each individual. The five exercise categories and exercises included in each category are shown in Table 1. The PT selects the timetable of the session and creates a progressive high-intensity program based on the pace of the patient. There are three intensity scales for both strength exercises, which depend on the sets of Repetition Maximum (RM) and the balance exercises where postural stability may be challenged close to the limit of maintaining postural stability (Table 2). A 5-min warmup of lower and upper limbs is applied while sitting before the balance exercises begin. Patients start the warmup with walking on the spot, opposing arm swings at the side of the body, “sewing-machine” steps, “picking apples” movement towards different directions, knee stretches, and steps to the side and back of both legs alternately. The equipment needed for the sessions is portable and consists of step boards and chair cushions (5 cm height min), weighted belts (1 kg), soft pads, mattresses and balls, bean bags, belts with handles, and chairs without arm support. All categories have various exercises for the PT to select (Table 1). Difficulty can be increased by providing less assistance or use softer surfaces. Strength intensity is enhanced with weight belt on A and D categories [18]. HIFE has been shown to improve balance, gait, and muscle strength among older persons who were dependent in activities of daily life [31].

Intervention B: the intervention comprises the HIFE rehabilitation protocol, and, if found necessary by the treating PT, other additional exercises. In addition, follow-up and feedback during the rehabilitation period will be given via an IMU, which participants wear 24 h per day until the rehabilitation period has ended (i.e., treatment goals are achieved). The treating PT is thereby provided with specific information regarding time spent per day in sitting, lying, and standing, the total amount of steps per day, any changes in walking speed, etc. Hence, follow-up and feedback can therefore include specific information from the PT to the patient regarding the progress of rehabilitation.

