### 2.5. Outcomes

The primary outcome is balance in terms of postural sway and functional balance. Measures of postural sway are performed with the patient standing with heels approximately 10 cm apart and feet pointing about 30° outwards for 30 s with eyes open (EO) and then 30 s with eyes closed (EC). During the measure, an IMU is mounted on the patient’s lower back, in level with L5. The IMU has shown good validity and reliability for measuring postural sway compared to the golden standard (force plate) [13]. Functional balance is assessed with the Functional Balance test for Geriatric patients (FBG), and grades the performance with points, where 0 stands for no execution and 6 for the higher level of performance. FBG evaluates the ability of the patient to sit and stand up, maintain a standing position, walk, and turn. The test includes four activities that the patient shall complete, and every activity has 7 levels of difficulty, indicating the level of independence in each task. The maximum points achievable is 24 [32]. The FBG has shown good validity and reliability when compared to the golden standard (Berg Balance Scale) [22].

Secondary outcome measures are functional independence in everyday activities, health-related quality of life, and the physiotherapist’s satisfaction with the IMU.

Functional independence in everyday activities will be assessed using The Barthel Activity of Daily Living questionnaire. Participants are asked how they manage various everyday activities such as food intake, locomotion, toilet visits, dressing, bathing, transferring, and continence. Ten activities are included, rated on a three-graded scale 0–2 with 0 indicating the worst condition/state and 2 the best condition/state. The maximum score is 20 [33].

Health-related quality of life will be measured by the EuroQol 5-Dimension Questionnaire (EQ5D). EQ5D is a generic instrument to measure mobility, self-care, everyday activities, pain, and anxiety, with five response alternatives, ranging from no problem to unable/extreme [34]. The EQ5D also consists of a visual analog scale, where the participant is asked to rate their health on a vertical scale, where 100 is the best imaginable health state, and 0 is the worst imaginable health state. EQ5D is widely used for monitoring health status among different patient groups all over the world [35].

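### Both follow-ups of the primary balance outcomes are timed from an individually tailored end of rehabilitation, so assessment time can differ by arm and distort the comparison in a direction and to a degree the protocol does not reveal

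*Protocol article*

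**What the plan says.** Section 2.5 defines the primary outcome: "The primary outcome is balance in terms of postural sway and functional balance". Section 2.6 sets its timing: "Follow-up measures will be performed at the end of the rehabilitation period, including primary and secondary outcome measures". The length of that period is individual: "The rehabilitation period is defined by the needs of the individual participant and can hence differ in time between participants". The only other assessment of balance depends on the same date: "Postural sway and balance will also be assessed 3 months after the end of the rehabilitation period".

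Section 2.4 applies this to all three groups by design: "the rehabilitation time periods are tailored to each participant in order to adjust the study to a clinical setting". In the text for Intervention B, participants wear the monitoring device "until the rehabilitation period has ended (i.e., treatment goals are achieved". For the control group, the same section bases treatment partly on treatment goals. It also announces a later limit, without a value: "a minimum number of sessions as well as a time interval for the rehabilitation period will be defined after analysis of the results" of the pilot.

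Section 2.9 compares the groups by ANOVA or Kruskal-Wallis and states no term for assessment time.

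**The concern.** Patients recover balance after a hip fracture whether or not the programme helps, so a balance score means little without the time at which it was taken. Here no primary assessment is tied to randomisation, surgery or discharge. The clock stops when rehabilitation ends, and the interventions are meant to influence the course of rehabilitation. In Intervention B the treating physiotherapist also sees continuous progress data that the other arms do not supply, so decisions about ending rehabilitation could differ by arm for that reason alone.

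Two opposite distortions are possible. An arm that speeds recovery may be measured earlier, so that its benefit appears as shorter rehabilitation and not as better sway or functional balance. An arm that is kept longer gains extra weeks of natural recovery before it is measured. Either way, the contrast mixes an effect on balance with a difference in timing. Fixed-time values that were never collected cannot be recovered in the analysis.

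**Working it through.** **The plan's own figure.** Section 2.7 gives 43 per group for 1.8 mm/s at alpha 0.017 and 80% power. It gives no SD, so 43 cannot be reproduced independently. Solving n = 2(z₁ + z₂)²SD²/δ² for SD, two-sided (sidedness is not stated): SD = 1.8 × √(43/2) / (2.387 + 0.842) ≈ 2.58 mm/s. The other steps agree: 0.05/3 = 0.0167, and 43/0.9 = 47.8, rounded up to 48. With this SD and n = 43, power is 80% for the full 1.8 mm/s, and 52%, 22% and 6% if timing leaves 75%, 50% or 25% of it.

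**Assumed recovery curves (not from the protocol).** Sway(t) = 6 + 9e^(−rt) mm/s, t in weeks, with r = 0.10 in control and 0.15 in the better arm. Both start at 15 and approach 6. The difference at a fixed date is:
- week 8: 10.04 − 8.71 = 1.33
- week 9: 9.66 − 8.33 = 1.33
- week 21: 7.10 − 6.39 = 0.72

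**End of rehabilitation unrelated to sway.** Let the end time be normal with mean 9 and SD 3 weeks in control. Mean sway is then 6 + 9exp(−rμ + r²σ²/2), which is 9.83 in control. In the better arm, mean and SD are scaled together. Losses are against 1.33 at fixed week 9.

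| Better arm ends | Its mean sway | Difference | Loss |
|---|---|---|---|
| at the same time | 8.58 | 1.25 | 6% |
| 10% earlier | 8.90 | 0.93 | 30% |
| 20% earlier | 9.26 | 0.57 | 57% |

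The loss grows with any further shortening. It is complete when rehabilitation shortens in the same proportion as recovery speeds up (one third earlier, since 0.15 × 6 = 0.10 × 9).

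**End of rehabilitation driven by sway itself (extreme case).** Suppose rehabilitation stops at the first weekly value below 9 mm/s. Without noise, control stops at week 11 (9.00) and the better arm at week 8 (8.71). The difference is 0.29 against 1.33 at fixed week 8, a loss of 78%. With reading noise of SD 1 mm/s the difference is about 0.23, a loss of about 82 to 83%.

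**The later visit in that extreme case.** Thirteen weeks after stopping: control at week 24, 6.82; better arm at week 21, 6.39. The difference is 0.43 against 0.72 at fixed week 21, a loss of 40%. With noise it is 0.46 to 0.48, a loss of about one third (33 to 36%).

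**Opposite direction.** With identical recovery (r = 0.10), measuring one arm at week 10 and the other at week 8 gives 9 × (0.449 − 0.368) = 0.73 mm/s from timing alone. That is 0.73/1.8 = 41% of the design difference.

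**A case with almost no loss.** If treatment lowers the plateau by 1.8 mm/s and timing is equal by arm, the difference is 1.8 × (1 − 0.425) = 1.03, against 1.8 × (1 − 0.407) = 1.07 at fixed week 9. About 3% is lost.

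**Effect of an upper limit on the period.** A separate simulation used an arm recovering twice as fast, with individual goals set as a share of the recoverable sway deficit. It gave 1.82 mm/s at a fixed 10 weeks and about 0 when measured at goal attainment. Capping the period at 16 or 12 weeks gave 0.39 or 0.90 mm/s. The caps are illustrative only.

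**The case against.** A reader might infer that every arm is measured at the same functional state, that about 80% of any effect disappears, and that the trial is biased toward no difference. The protocol does not support this. It describes no weekly sway reading: section 2.3 takes sway at baseline and follow-ups only, and the monitoring device in Intervention B is a different one, worn on the thigh, reporting positions and movements. Goals are individual and are nowhere defined as a sway or functional balance threshold. The text equating the end of rehabilitation with achieved goals appears only under Intervention B, and no section says who declares goals met. The 80% belongs to one extreme scenario, and the bias can also favour an arm.

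Other points also carry weight. Tailoring is deliberate, and outcome at discharge from rehabilitation is a coherent pragmatic question. A time interval is promised, and sections 2.6 and 2.10 allow changes after the pilot. Home visits and calls are recorded and compared, so a faster course would not go unseen. The later visit is less sensitive to timing, and section 2.8 plans an independent, unaware assessor for it once restrictions lift.

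These points limit the size of the concern but leave the mechanism in place. Tailoring treatment length does not require tailoring assessment time. An interval bounds the spread without fixing the date. Visits and calls are not the primary outcome, and the later visit inherits the floating date. Goals need not be sway scores: it is enough that an intervention shortens rehabilitation as well as improving balance.

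**Conclusion.** The concern holds as a design weakness of uncertain size. Both assessments of the primary outcome occur at a time set after randomisation, which can depend on recovery and on arm, and the stated comparison takes no account of it. Under the assumed curves, the loss at the end-of-rehabilitation visit runs from about 6% to about 80%, with 30 to 57% if the better arm finishes 10 to 20% earlier. At the visit 3 months later it is about 35 to 40% in the sway-driven scenario. These figures are illustrations and not bounds. They rest on assumed recovery rates, a shared plateau and assumed rehabilitation lengths, and they concern sway only. If an arm is kept longer, the error runs the other way. This should be fixed before the full trial.

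**What to change.** When the post-pilot interval is set, schedule both primary assessments at fixed times from randomisation, with a stated window, identical in all arms and carried out whether or not rehabilitation has ended. Choose the times from the pilot's distribution of rehabilitation length. Leave the length of rehabilitation as it is, and compare time to end of rehabilitation between arms as a separate secondary outcome, so that a faster course is visible in its own right.

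The cost is protocol wording and visit scheduling; the number of assessments does not change. The drawbacks are that some participants will still be in rehabilitation at the first date, and some assessments will not coincide with a treatment visit.

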### 2.7. Sample Size

Since balance, measured by postural sway, is the main outcome measure, postural sway was used to determine the statistical power of the study. We used results from a previous study [25] with a mean value of 1.8 mm/s for difference in postural sway in the anterior-posterior (AP) direction between two groups of community-dwelling older persons. Since we want to calculate differences between all three groups, a significance level of 0.017 was determined, giving a necessary sample size of 43 participants in each group to reach a power of 80% [37]. To compensate for dropouts, the sample size was set to 48 participants in each group.

### 2.8. Randomization

To enhance the power of the study, to reduce bias of covariates and ensure equal dispersion of the participants at all times [38], block randomization will be applied through a website [39]. The number of subjects in each block will be 48 and the number of blocks will be 3, generating a randomization plan with subjects randomized in 3 different treatment blocks.

An independent person will perform the randomization process. All baseline measures will be performed before randomization to any of the interventions. Blinding of the assessor is not possible at present, due to the restrictions caused by the Covid-19-pandemic, prohibiting unnecessary home visits. However, when these are lifted, follow-up measures at 3 months will be performed by an independent PT, not aware of which intervention the participants have been allocated to. Blinding of participants is not considered possible.

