The use of tailored intervention protocols towards patients’ needs and capabilities is recommended, with a focus on balance and proprioceptive endurance together with physical and mental independence [16]. A patient-centered intervention is needed, as individuals with a hip fracture will differ in many aspects, such as pre-fracture medical history and activity, type of surgery, and capability to recover [5,16]. The High-Intensity Functional Exercise (HIFE) program was developed specifically for frail older patients with hip fracture [17], aiming at improving muscle strength, balance, gait, and mobility [18]. HIFE is a person-centered intervention protocol, with exercises chosen for each individual after assessment by a physiotherapist. The program is regularly adapted during the rehabilitation period. HIFE has been evaluated among persons with dementia [19] and among persons living in nursing homes [20], but has to our knowledge not been evaluated when applied to rehabilitation in community health care.

RCT’s studying the effect of rehabilitation after hip fracture are few [11], and their external validity has been questioned as they are performed within a strict protocol [21]. Hence, RCT’s applying tailored intervention protocols, such as HIFE, might increase the usefulness of results from such an RCT in clinical practice.

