### 2.9. Statistics

Differences between the three groups will be analyzed. Normally distributed data will be analyzed using ANOVA and on abnormally distributed data, the Kruskal-Wallis test will be applied [37]. The ANOVA test will show if there is a significant difference between the groups and a post-hoc analysis will detect where the difference lies. In all analysis, intention to treat will be used.

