This study protocol does not include any specific measure of muscle strength. However, functional balance, here measured in the FBG test, demands muscle strength and so does functional independence in everyday activities, here measured with the Barthel questionnaire. Strength has a relation to dependence in everyday activities [48]. Baseline measurers will be performed shortly after discharge from the hospital and a measure of muscle strength can therefore be highly influenced by pain. Additionally, we want to limit the total number of tests, since performing them can be physically challenging.

In intervention B, in addition to HIFE, data of body positions and movements are collected using an IMU. Data is collected via the IMU 24 h per day and transferred through an application to the treating PT giving him/her an opportunity to follow the participants’ progression in the rehabilitation process on a day-to-day basis. This also enables the PT to provide constructive feedback to the participants during the monitoring period. Wearable devices with a built-in accelerometer have shown the ability to provide accurate data with individual characteristics [49]. Laboratory, as well as home-based studies, have shown that accelerometer technology can accurately evaluate balance and risks of falls in an older population [50]. However, whether this has any effect on the outcomes of rehabilitation has, to our knowledge, not been studied before. In addition, concerns regarding patient privacy, management of system operation, and the magnitude of data need to be evaluated carefully before the use of these type of devices [51].

The study will evaluate the balance of the participants via postural sway and FBG tests. The FBG test, specifically designed for older people, will evaluate the static and dynamic balance and participant’s gait. Wearable devices make it possible to measure postural sway outside the laboratory setting, and an IMU is easy to transport and easy to use. Thus, the IMU is a novel tool for assessing postural sway in a clinical setting.

Randomization will be performed with block randomization to ensure an equal number of participants in each group. We expect that there might be more dropouts from the intervention including monitoring with an IMU. Therefore, we made a generous calculation of the dropout rate when calculating the sample size.

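### Blocking is justified partly by covariate balance, but the blocks described are unstratified and protect against imbalance in surgery type, age or sex no better than simple randomisation

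*Protocol article*

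**What the plan says.** Protocol article, 2.8 Randomization, states three purposes for the allocation method: "To enhance the power of the study, to reduce bias of covariates", and to keep the groups evenly filled throughout recruitment. The method is then given as "block randomization will be applied through a website", with "The number of subjects in each block will be 48 and the number of blocks will be 3". No stratification or minimisation factor is named. The same section places all baseline measures before randomisation.

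The Discussion (section 3) gives one purpose only: "Randomization will be performed with block randomization to ensure an equal number of participants in each group".

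The Introduction notes that "individuals with a hip fracture will differ in many aspects, such as pre-fracture medical history and activity, type of surgery, and capability to recover". Section 2.6 says: "Background data on age, sex, method of surgery for the hip fracture, and medication will be collected at baseline". Section 2.9 describes the comparison of the three groups: "Normally distributed data will be analyzed using ANOVA and on abnormally distributed data, the Kruskal-Wallis test will be applied".

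**The concern.** Blocking acts on the order of assignments. It looks at no patient characteristic, so without strata it cannot steer surgery type, age or sex towards balance. A stated reason for the design is therefore one that the design does not deliver, and the Discussion does not repeat it.

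What is at stake is modest. A reader may take covariates to be protected by design when they are left to chance. The sponsor may also see no reason to use a baseline factor that is already in hand before allocation. A chance imbalance in a prognostic factor enters an unadjusted comparison as noise that a model term would remove.

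**Working it through.** **Inputs from the documents.** 144 participants in three arms of 48 (2.1, 2.7); three blocks of 48 (2.8); difference of 1.8 mm/s, significance level 0.017, power 80%, 43 per group before dropout (2.7).

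**Assumptions.** Prevalence of a binary prognostic factor: 50%, with 30% as a second case. Effect of the factor on sway: 0.5 SD. The documents give neither of these, nor the SD of sway.

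**1. The plan's own figure.** Without an SD, the 43 per group can be neither confirmed nor refuted. Solved backwards with a two-sided test, n = 2(z_α/2 + z_β)²·SD²/1.8² = 43 gives SD = 2.59 mm/s by the normal approximation, and 2.54 mm/s by the t-test. These values are used below for scale only.

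**2. Power gain from equal arms.** Under simple randomisation an arm size has SD √(144 × 1/3 × 2/3) = 5.7; under the blocks it is 0. With SD 2.59 and an average of 48 per arm, power for one pairwise comparison is 84.7% with equal arms and 84.1% with simple randomisation. The gain is about 0.6 points.

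**3. Covariate balance with 48 per arm.** With prevalence p, the SD of the difference in share between two arms is √[(144/143) × p(1 − p) × 2/48].
- p = 50%: √[(144/143) × 0.25 × 2/48] = 0.102, or 10.2 points.
- p = 30%: 9.4 points.

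With 72 carriers among 144 allocated at random to three arms of 48 (simulation), a gap of at least 15 points means 8 or more patients, and a gap of at least 20 points means 10 or more.

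| Gap in share, p = 50% | Some pair of arms | One given pair |
|---|---|---|
| 15 points or more | 28% | 13% |
| 20 points or more | 13% | 5% |

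**4. Blocks against simple randomisation.** 15,000 simulated trials per setting, factor unrelated to entry time.

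| Scheme | Mean largest gap, p = 30% | Mean largest gap, p = 50% | Some pair 20 points or more apart, p = 50% |
|---|---|---|---|
| Simple | 11.2 points | 12.2 points | 12% |
| Three blocks of 48 | 11.2 points | 12.2 points | 13% |
| Blocks of 6 within strata of the factor | 1.5 points | 1.4 points | about 0% |

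The blocks add nothing on this measure.

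**5. Where the blocks do help.** For a factor that switches halfway through recruitment, the chance that some pair differs by 15 points or more falls from 32% (simple) to 2% (three blocks of 48).

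**6. Consequence for the comparison.** On the assumed effect, a 20-point gap moves an arm difference by 0.20 × 0.5 × 2.54 = 0.25 mm/s, or 14% of 1.8. The standard error of a pairwise difference is 2.54 × √(2/48) = 0.52 mm/s, so the shift is about half a standard error.

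**7. Gain from adjustment.** The factor explains 0.5² × 0.25 = 6.25% of the variance, so the residual SD is 2.54 × √0.9375 = 2.46. By the normal approximation, power at 48 per arm rises from Φ(1.8/0.5185 − 2.387) = 86.1% to Φ(1.8/0.5020 − 2.387) = 88.5%. At 43 per arm it rises from 81.6% to 84.3%. The gain is 2 to 3 points.

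**The case against.** The case for leaving the plan as it is has several sound parts.

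- **Unstratified blocked randomisation is valid.** Chance imbalance is already contained in the standard error and the type I error. A reader might infer that the group comparison is biased. It is not: randomisation removes systematic covariate bias, with or without strata.
- **Blocks do more than fix arm sizes.** They limit calendar drift (step 5), which matters because section 2.8 itself describes pandemic restrictions that are expected to change.
- **The power statement is true.** The gain is small, but it exists.
- **No balance on surgery type is promised.** A reader might infer such a promise, but section 2.8 names no covariate; surgery type is only an example here. Nor does the Introduction call it a cause of better or worse recovery. It lists type of surgery and capacity to recover side by side as ways in which patients differ.
- **The size depends on the comparison.** The 13% is for the worst of three pairs. For one given pair it is 5%, so a gap of 20 points should not be called common.
- **The analysis section is a summary in an article.** A full protocol or analysis plan that is not shown may hold covariate adjustment. It cannot be concluded that surgery type is ignored in the analysis.

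All of this stands. It confines the point to one clause of the rationale and to some recoverable precision. None of it makes covariate balance a property of the blocks described.

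**Conclusion.** The point holds in a limited form. As described, the allocation does not reduce covariate imbalance beyond what simple randomisation does, except for factors tied to calendar time. The covariate reason in section 2.8 is therefore wrong for surgery type, age, sex and the like, while the power reason is correct but small (about 0.6 points).

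The cost is chance imbalance, with a pairwise SD of about 10 points at 50% prevalence, and about 2 to 3 points of power that adjustment for a factor worth 0.5 SD would recover. Validity, type I error and sample size are unaffected. The imbalance figures rest on the assumed prevalence. The power figures rest on an assumed effect of the factor and on an SD back-solved from the sample size; none of these is stated in the documents.

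**What to change.** Include method of surgery, as recorded before randomisation, in the primary model as a prespecified factor alongside treatment arm. The sponsor would need to define its categories in advance. The Kruskal-Wallis route takes no covariate, so the primary analysis has to be a model that can carry the term.

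Optionally, stratify the allocation list by method of surgery with small blocks within strata; the factor then stays in the model.

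If the list is not stratified, remove the covariate-balance rationale from section 2.8. The power statement may stay if it is described as a small gain from equal arm sizes. Deleting the wording alone would correct the text but gain nothing for the trial.

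The cost is one model term. With stratification there is also slight extra administration and possibly one unfinished block per stratum. Sections 2.6 and 2.10 allow changes to the protocol after the pilot and before the full trial, so there is time to make it.
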